## Abstract

**Background:**

Tuberous sclerosis complex (TSC) is a genetic disorder affecting about 1 in 6000 people and is characterised by the development of tumours in many organs, including the skin and kidneys, and by a range of neurological and neuropsychiatric manifestations. TSC-associated neuropsychiatric disorders (TAND) occur in the majority of those with TSC, and they have a significant impact on patients and their families, given the everyday impact of TAND on education, employment, family and social life. The potential benefits of better treatment for TAND therefore include reduction in health care demands and wider benefits for patients and their carers.

**Methods/design:**

We have planned a single-centre, two-arm, individually randomised, phase II, double-blind, placebo-controlled trial of everolimus versus placebo in the treatment of neurocognitive problems in patients with tuberous sclerosis. Everolimus is a licensed medicine in this patient group, but for a different target of effect. The present trial is a proof-of-principle study developed to provide effect size estimates which may be used to inform the design of subsequent trials. Forty-eight patients aged 16–60 years with tuberous sclerosis who have an IQ >60 and a significant deficit (at least −2 SD) in one or more primary outcome measures will be randomly allocated in a ratio of 2:1 to receive everolimus or placebo, respectively. Participants will be assessed for eligibility and then be started on study medication 4 weeks later. They will then be randomised and receive placebo or everolimus for 24 weeks. Neurocognitive and safety assessments will be carried out at baseline and weeks 4, 12, 24 and 36.

**Discussion:**

This study is designed to determine the effect sizes of treatment with everolimus or placebo for 6 months on specific neurocognitive functions—recall memory (verbal and non-verbal) and executive function—in people affected by TSC who have significant deficits in these functions. These data will provide new evidence to determine whether larger-scale trials are indicated and to explore suitable outcome measures and analytical methods for neurocognitive trial design.

**Trial registration:**

ISRCTN09739757. Registered on 28 Dec 2011.

**Electronic supplementary material:**

The online version of this article (doi:10.1186/s13063-016-1446-6) contains supplementary material, which is available to authorized users.

## Background

Tuberous sclerosis complex (TSC) is a rare genetic disorder affecting approximately 1 in 6000 people and is caused by mutations in the *TSC1* or *TSC2* gene. It is characterised by the development of benign tumours in many organs, including the skin, kidneys, heart, eyes, lungs and brain. Brain involvement can lead to seizures, neurocognitive deficits and behavioural and developmental disorders. TSC-associated neuropsychiatric disorders (TAND) occur in the majority of those with TSC, even in the approximately 50 % of patients with normal IQ (>70) [1–3], and they are rated as the most significant disease manifestations by patients and families because of their everyday impact on education, employment, family and social life [4]. Better treatment options for TAND have the potential to both reduce health care demands and offer wider benefits for patients and their carers.

In the past, it was thought that the cognitive, behavioural and neurological manifestations of TSC might be entirely attributable to tubers—characteristic areas of cerebral cortex or sub-cortical white matter—which occur in most people with TSC. However, recent molecular and cellular insights indicate that the intracellular consequences of *TSC1* and *TSC2* gene mutations may also play a direct and potentially reversible role [5]. New imaging techniques have revealed subtle abnormalities of brain microstructure in otherwise normal-appearing white matter [6]. The TSC1 and TSC2 proteins (hamartin and tuberin, respectively) form a complex that acts to suppress mammalian target of rapamycin complex 1 (mTORC1) signalling; thus, disruption of the TSC1-TSC2 complex (as a consequence of mutations in either *TSC1* or *TSC2*) leads to excessive mTORC1 signalling. The effects of this have been demonstrated in immunohistochemical and immunoblotting studies that have shown activation of the downstream effectors of mTORC1, S6 kinase and phospho-S6 in tuberous sclerosis lesions in both pre-clinical models and patients [7]. In pre-clinical trials, treatment with mTORC1 inhibitors shrank or prevented kidney tumours, improved memory and learning, stopped or prevented epilepsy, and improved survival in transgenic *Tsc1*- and *Tsc2*-mutant mice [8–10]. Published findings from the *Tsc2* study [9] came at a time which served to reinforce interest in the neurocognitive trials in humans. Clinical trials using the mTORC1 inhibitors sirolimus and everolimus have demonstrated significant reductions in brain and kidney tumour volume, along with acceptable safety and tolerability, in patients with tuberous sclerosis [11–15]. These findings led to licensing of everolimus for these indications in the United States and Europe.

In the study of Davies et al. [13, 14], we also monitored memory, learning and executive function as secondary endpoints. During the treatment period, patients with tuberous sclerosis showed improvements in visuospatial and verbal recall memory and in executive function, but not in recognition memory tasks. However, because the trial was not a randomised controlled trial and involved very small numbers of patients, we could not distinguish learning effects due to repeat administration (so-called practice effects) of the tests from drug effects.

Up until 14 September 2015, a total of 11 controlled trials of investigational medicinal products investigating mTORC1 inhibitors in patients with tuberous sclerosis were listed at ClinicalTrials.gov. Several are completed or no longer recruiting. Most are investigating tumour-related outcomes. All are using everolimus or sirolimus (rapamycin). Researchers in one current phase II, non-randomised, open-label trial are investigating the efficacy of everolimus in TSC-associated seizures (NCT01070316). A signal-seeking, randomised, placebo-controlled trial of everolimus for neurocognitive problems in young people with TSC has been completed in the United States, but the results are not yet reported (NCT01289912) [3].

The present trial, TRON, will be an investigation of everolimus in relation to neurocognitive function in adult patients with TSC. It will determine effect sizes to provide evidence for whether larger trials for this indication are appropriate. In contrast to the U.S. study (NCT01289912), it will be focused on adult patients who do not have active seizures or who have well-controlled seizures as well as some degree of cognitive impairment. TAND is multi-level with varying cognitive, behavioural and psychiatric manifestations [3]. In order to differentiate between these, the principal level investigated here through the primary outcomes is the ‘neuropsychological’ level, which will be referred to as *neurocognition*.

## Methods/design

### Study design

This is a single-centre, two-arm, individually randomised, phase II, double-blind, placebo-controlled trial of everolimus versus placebo (allocation ratio of 2:1, respectively) in the treatment of neurocognitive problems in patients with TSC. Patients are treated in an outpatient setting at a specialist centre in a large teaching hospital. The present trial is a proof-of-principle study designed to provide effect size estimates which may be used to inform the design of subsequent trials (Fig. 1). Ethical approval was granted by the Wales Research Ethics Committee on 9 November 2011. A Standard Protocol Items: Recommendations for Interventional Trials (SPIRIT) checklist is provided as Additional file 1.

**Fig. 1 Fig1:**
[figure not shown]
TRON trial design flowchart indicating anticipated patient numbers and dropout. *CRN* Clinical Research Network, *DTI MR* diffusion tensor imaging magnetic resonance imaging, *PIS* patient information sheet, *TSA* Tuberous Sclerosis Association

### Research objectives

#### Primary objective

The primary objective is to determine the effect sizes of treatment with everolimus or placebo for 6 months on recall memory and executive function in people with tuberous sclerosis.

#### Secondary objective

The secondary objective is to assess the effects of treatment with everolimus or placebo for 6 months on wider aspects of neurocognitive functioning, seizures and daily life in people with tuberous sclerosis and to assess safety using the National Cancer Institute Common Terminology Criteria for Adverse Events (CTCAE) version 4.0.

#### Exploratory objective

A further exploratory objective is to determine whether an effect of treatment with everolimus or placebo is detectable at 1 month and 3 months after the start of therapy to establish whether any early markers of change are present.

### Sample size determination

The sample size has been calculated on the basis of Fleming’s single-stage procedure [16] and considers the sample size required to assess the change in the experimental group. The control group provides evidence of the learning effect due to repeated assessments. The proposed study seeks to determine effect sizes in relation to the primary outcome measures to enable informed designing of subsequent larger studies. This study is therefore not powered for formal statistical comparison of placebo and study drug groups.

We estimate the learning effect (i.e., the proportion of patients whose memory function improves due to familiarity with the assessments) to be slightly less than 0.15. A proportion of less than 0.15 in the intervention group would therefore indicate that the intervention (everolimus in the treatment of neurocognitive problems in tuberous sclerosis) does not warrant further investigation. A proportion of at least 0.35 would provide sufficient evidence for further investigation of this intervention. Values between these would be discussed in depth by members of the trial team.

Therefore, to test the null hypothesis that the proportion of patients in the intervention group who improve their memory function by 1 SD is at most 0.15 against the alternative hypothesis that the proportion of patients in the intervention group who improve their memory function by 1 SD is at least 0.35, with 80 % power and a one-sided α of 0.05, we require a total sample size of 48 (i.e., 32 who receive the intervention and 16 control subjects). This sample size is inflated to allow for 20 % loss to follow-up.

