### Statistical methods

#### Main analysis

All randomised participants who received at least one dose of study drug will be included in the data analysis. Patients will be analysed according to the treatment they received. We will present data descriptively and determine effect sizes. Results will be presented split by trial arm.

The primary outcome of this study is memory function with improved memory function classed as a 1-SD response on any of the memory tests listed in Table 3. A one-sample chi-square test will be used to determine whether the proportion of patients in the intervention group with improved recall memory at 6 months by 1 SD is at least 0.35. The effect size will be presented alongside a 95 % CI and *p* value. The proportion of patients in the control group displaying improved functioning by 1 SD will be used to highlight the learning effect.

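### At the planned 20% loss, the stated 80% power and one-sided alpha of 0.05 cannot both hold for the everolimus-arm test

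*Protocol article*

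**What the plan says.** In the protocol article, the section on sample size determination names its method: "The sample size has been calculated on the basis of Fleming’s single-stage procedure". The null is that the proportion of everolimus patients improving by 1 SD "is at most 0.15 against the alternative hypothesis", and the alternative is that the proportion "who improve their memory function by 1 SD is at least 0.35". The design is stated "with 80 % power and a one-sided α of 0.05", and the conclusion is "we require a total sample size of 48 (i.e., 32 who receive the intervention and 16 control subjects". The section adds: "This sample size is inflated to allow for 20 % loss to follow-up".

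The same section disclaims power for the comparison of drug with placebo. It also sets out three zones for the proportion: below 0.15, no further investigation; 0.35 or above, sufficient evidence to continue; in between, discussion by the trial team.

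The main analysis section fixes the test: "A one-sample chi-square test will be used to determine whether the proportion of patients in the intervention group" reaches 0.35. It states no sidedness and no continuity correction. Neither section gives a critical number of responders.

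**The concern.** The number 32 is described as already inflated for 20% loss, so the claimed power and alpha have to hold at about 25 or 26 evaluable everolimus patients. At that size only 3.75 to 3.9 responders are expected under the null. The outcome is a count, and one responder more or less moves both error rates by several percentage points. A normal or chi-square approximation is unreliable in this range.

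This is the only test in the article for which a power and an alpha are stated. If the two figures cannot hold together, readers of the result will misjudge either how likely the test was to detect a true rate of 0.35, or how strong the evidence is when it rejects 0.15.

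**Working it through.** **Inputs**, all from the sample size section: p0 = 0.15, p1 = 0.35, one-sided alpha 0.05, power 80%, 32 everolimus patients, 20% loss. Normal quantiles: 1.645 and 0.842.

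**Step 1: reproduce the plan's figure.** The one-sample large-sample formula is

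n = [(1.645·√(0.15·0.85) + 0.842·√(0.35·0.65)) / (0.35 − 0.15)]² = 24.4, rounded up to 25.

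Inflation for loss: 25/0.8 = 31.25, rounded up to 32. With 16 controls at 2:1 the total is 48. The plan's number is reproduced. The same approximation puts power at 80.7% for n = 25 and 81.8% for n = 26.

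**Step 2: evaluable number at the planned loss.** 32 × 0.8 = 25.6, so 25 or 26.

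**Step 3: exact binomial properties.** With X the number of responders, alpha = P(X ≥ k | 0.15) and power = P(X ≥ k | 0.35).

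| Evaluable n | Reject if X ≥ | True alpha | Power |
|---|---|---|---|
| 25 | 7 | 0.0695 | 0.827 |
| 25 | 8 | 0.0255 | 0.694 |
| 26 | 7 | 0.0833 | 0.858 |
| 26 | 8 | 0.0321 | 0.740 |

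A cut-off below 7 raises alpha further, and one above 8 lowers power further. So no cut-off at either size gives alpha ≤ 0.05 together with power ≥ 80%.

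**Step 4: which cut-off a chi-square test would use.** Tested against 0.15, one-sided and uncorrected, the critical point is n·p0 + 1.645·√(n·p0·0.85). This is 6.69 at n = 25 and 6.89 at n = 26, so the test rejects at 7. A continuity-corrected one-sided test, or a two-sided 5% test, rejects at 8 for both sizes.

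**Step 5: exact power across the possible evaluable numbers**, using the smallest cut-off with alpha ≤ 0.05.

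| Evaluable n | Cut-off | Alpha | Power |
|---|---|---|---|
| 25 | 8 | 0.026 | 69% |
| 26 | 8 | 0.032 | 74% |
| 27 | 8 | 0.040 | 78% |
| 28 | 8 | 0.049 | 82% |
| 29 | 9 | 0.022 | 74% |
| 30 | 9 | 0.028 | 78% |
| 31 | 9 | 0.034 | 81% |
| 32 | 9 | 0.041 | 84% |

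Power does not rise steadily with n: it falls when the cut-off steps from 8 to 9. If each of the 32 patients is independently evaluable with probability 0.8, the power averaged over the resulting n is 73%.

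**The case against.** The strongest reply is that 48 is correct by the method used, that the article names a procedure without promising exact power, and that this is a proof-of-principle study meant to yield effect sizes with a 95% CI. It is true that there is no slip in the arithmetic, and a reader who inferred one would be wrong. The study's purpose also lowers the stakes. But the power disclaimer covers only drug versus placebo. For the everolimus arm, a power and an alpha are stated, and getting 48 from an approximation does not make them jointly true at the planned evaluable number.

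Three stronger readings are tempting and are not supported.

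- *That the chance of missing a worthwhile drug is 26% to 31%, or the false-go rate 7% to 8%.* The three-zone rule breaks this link. Read as observed proportions, 7 or 8 responders are 28% or 32% of 25, and 27% or 31% of 26. All fall in the discussion zone. Under that reading, an outright stop (3 or fewer responders) at a true rate of 0.35 has probability 0.010 (n = 25) or 0.007 (n = 26). An outright go at a true rate of 0.15 has probability 0.008 (9 or more of 25) or 0.003 (10 or more of 26).
- *That the planned chi-square test runs at 7% to 8% error.* This needs a one-sided, uncorrected test against 0.15. The main analysis section specifies none of these and words the question around 0.35.
- *That 32 patients tolerate 12.5% loss because 28 evaluable gives 82% power.* Power is below 80% at 29 and 30, so losing only two or three patients already breaks the claim.

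The article cites Fleming's procedure but gives no cut-off formula from it, so nothing here rests on one.

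**Conclusion.** The point holds as a statement about the hypothesis test. At 25 or 26 evaluable everolimus patients, the plan can have alpha within 0.05 with 69% to 74% power, or at least 80% power with a true alpha of 0.070 to 0.083, but not both. The cause is a large-sample approximation applied where it is inadequate.

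This rests on the article's own 0.15, 0.35, alpha, power and 20% loss, on independent patients, and on the loss actually occurring. With all 32 evaluable, both targets are met (alpha 0.041, power 84%). With alpha held at 0.05 or below, power reaches 80% at 28, 31 and 32 evaluable patients and falls short at 25, 26, 27, 29 and 30.

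**What to change.** In the sample size section, replace the single power claim with exact power by evaluable number at one-sided alpha of at most 0.05: 25: 69%, 26: 74%, 27: 78%, 28: 82%, 29: 74%, 30: 78%, 31: 81%, 32: 84%. State that 80% power is not assured at the planned 20% loss. Give every value, since a selection would hide the dip at 29 and 30.

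In the main analysis section, replace the one-sample chi-square test with a one-sided exact binomial test against 0.15. The cut-off should be the one for the number actually evaluated: 8 or more responders for 25 to 28 patients, 9 or more for 29 to 32.

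Both are changes of wording and need no extra patients. The cost is a less favourable stated power. If the sponsor wanted 80% to hold at exactly 20% loss, 28/0.8 = 35 everolimus patients would be needed, about 53 in total at 2:1 (54 as 36 + 18), and the dip at 29 and 30 would remain. The restatement does not depend on that.

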### Recruitment

Patients aged between 16 and 60 years with tuberous sclerosis will be invited to take part in the trial. The trial will be advertised through the Tuberous Sclerosis Association (TSA) via its website, a regular update e-magazine and a magazine that is mailed to TSA members (approximately 1000 families). Clinical geneticists throughout the United Kingdom will be made aware of the study through the Clinical Genetics Clinical Research Network, and the study has been adopted by National Institute for Health Research via this network. Awareness of the trial will be raised at appropriate conferences. Genetics services will be approached to act as patient identification centres. Patients attending TSA-supported tuberous sclerosis clinics will also be notified of the trial.

### Screening for eligibility

Entry into the study is carried out through a two-stage process. Those who are likely to be eligible will be offered a screening appointment (visit 1), at which fully informed written consent will be obtained. A screening assessment to confirm or refute eligibility will include a full medical history; current medications; physical examination; blood, urine and (for females) pregnancy tests; and neurocognitive tests. Patients must fulfil all of the inclusion criteria and none of the exclusion criteria, as detailed in Table 1.

**Table 1 Tab1:** TRON study entry criteria

	Inclusion criteria	Exclusion criteria^a^
1	Definite TSC based on current clinical criteria [29]	Prior treatment with an mTOR inhibitor
2	Male or female aged 16–60 years	Investigational agent taken <30 days prior to randomisation
3	IQ >60 as determined by using WASI and able to participate in direct neuropsychological tests	Surgery in last 2 months
4	A score falling on, or below, the 5th percentile (approximately equivalent to −1.5 SD) in one or more of the primary outcome measures	Previous brain neurosurgery, with the exception of sub-ependymal giant cell astrocytoma removal surgery or radiosurgery 5 or more yearsv ago
5	Calculated GFR >60 ml/min/1.73 m^2^, except in case of renal impairment associated with TSC kidney disease, in which event a calculated GFR should be ≥30 ml/min/1.73 m^2^	Significant haematological abnormality (i.e., haemoglobin <8 g/dl, platelets <80,000/mm^3^, absolute neutrophil count <1000/mm^3^)
6	INR ≤1.5 (anti-coagulation permitted if target INR on stable dose of warfarin or LMW heparin for >2 weeks at time of randomisation)	Urine protein/creatinine >0.02 g/mmol, except in case of renal impairment associated with TSC kidney disease, in which case urine protein/creatinine ratio should be >0.1 g/mmol for exclusion
7	Adequate liver function as shown by serum bilirubin ≤1.5 times ULN, ALT and AST ≤2.5 times ULN	Serum creatinine >1.5 times ULN, except in cases of renal impairment associated with TSC complication of kidneys, where serum creatinine should be >300 μmol/L for exclusion
8	If sexually active, negative pregnancy test in females at the time of informed consent, contraception for males and pre-menopausal females in the study	Uncontrolled hyperlipidaemia (fasting cholesterol >300 mg/dl or >7.75 mmol/L and fasting triglycerides >2.5 times ULN, or diabetes with fasting serum glucose >1.5 times ULN)
9	Seizure-free or stable seizures as defined by no change in type of AEDs in 6 months prior to full recruitment and randomisation at baseline; doses of drugs may have been changed in the 6 months prior to recruitment	History of myocardial infarction, angina or stroke related to atherosclerosis, or any other significant cardiac disease, HIV seropositivity, organ transplant, malignancy other than squamous or basal cell skin cancer
10	Hepatitis B surface antigen-negative, hepatitis C antibody-negative	Lymphangioleiomyomatosis with FEV_1_ < 70 % of predicted, or any other restrictive pulmonary disease
11	All patients must be able to communicate well with the investigator, to understand and comply with the requirements of the study, and to understand and sign the written informed consent form	Bleeding diathesis or on oral anti-vitamin K medication other than low-dose warfarin
12	Female patients of childbearing potential must be prepared to use two acceptable methods of contraception (e.g., intra-uterine device plus condom, spermicidal gel plus condom, diaphragm plus condom) from the time of screening	Pregnancy/lactation
13		Live vaccine required during trial
14		Use of strong inhibitor of CYP3A4
15		Use of strong inducer of CYP3A4, except for anti-epileptic drugs
16		Intercurrent infection at time of randomisation
17		Inability to complete study materials (outcome measures) in English
18		History of significant trauma-related cognitive deficit
19		Impairment of gastrointestinal function or gastrointestinal disease that may significantly alter the absorption of everolimus (e.g., pancreatic insufficiency)
20		Known sensitivity to everolimus or other rapamycin analogues or to its excipients
21		Inability to attend scheduled visits

*Abbreviations: AED* anti-epileptic drug; *ALT* alanine aminotransferase, *AST* aspartate aminotransferase, *CYP3AE* cytochrome P450 3AE, *FEV*
_*1*_ forced expiratory volume in 1 second, *GFR* glomerular filtration rate, *INR* international normalised ratio, *LMW* low molecular weight, *mTOR* mammalian target of rapamycin, *TSC* tuberous sclerosis complex, *ULN* upper limit of normal, *WASI* Wechsler Abbreviated Scale of Intelligence

^a^Patients meeting any of the exclusion criteria will be excluded from entry into or continuation in the study unless sponsor approval is obtained

